##### The case manager

The case manager is a fixed contact person; building a relationship is desirable because of the complexity of learning to live with ABI within the individual context, and to prevent the person with ABI and their family from having to tell their story over and over again. A back-up case manager will be assigned as well, who will be involved when the primary case manager is unavailable and who can serve as a sparring partner for the primary case manager.

The case managers form three teams, one in each region. Teams are composed of professionals from different disciplines and with varying backgrounds; some have been working in clinical/rehabilitation settings, others in community outreach, and their experience with support and treatment approaches may be focused on cure or on care. Two of the teams include a peer support worker.

Case managers will participate in a 4-day training prior to the start of the study. The training has a coaching character, promoting team members to draw upon each other’s knowledge and experience. During the training, case managers learn to see beyond one’s own specific professional discipline, get to know the professional background of the other team members and are coached in learning from each other to best support people with ABI and their family. Regular supervision meetings are organized with case managers within regions at least every 2 months, and between regions twice a year.

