#### Care as usual

The usual care differs depending on the regional structures and collaborations. In all regions, limited structured care is available for people who suffered a stroke, mostly for secondary prevention purposes, with a limited duration of 1 year. No structural care is provided for other types of ABI. People with ABI can make use of different forms of care that may or may not involve professionals with expertise on ABI, such as physiotherapy, occupational therapy or social work, but patients usually need to take initiative to find and access these services either themselves or through their general practitioner.

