## Assignment of interventions: allocation

### Sequence generation {16a}

Participants (people with ABI or people with ABI-family-member couples) will be randomly allocated with a 1:1 ratio to either the case management group or the care as usual group, using a computerized random schedule, in blocks of six. The randomization block size will not be disclosed to the research assistant who enrols and assess participants, to ensure concealment.

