## Statistical methods

### Statistical methods for primary and secondary outcomes {20a}

#### Effectiveness

Multilevel modelling will be used to assess the improvement of case management participants over time compared to care as usual. Primary analysis involves entering time, group and their interaction (exposure) as fixed terms. Separate analyses will be performed to assess 24-month outcomes for the subgroup of participants for whom this data is available. Sensitivity analysis will be performed by extending the resulting models with covariates, controlling for the effects of age, gender and level of education. Covariates will be kept in the model as long as they contribute significantly to the model. Significance of the fixed regression effects will be tested using the appropriate *t*-test (*α* = .05).

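### The covariate-adjusted sensitivity model is chosen by significance, and the primary model names neither region nor the baseline HADS score that the sample size relies on

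*Protocol article*

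**What the plan says.** All references are to the protocol article.

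- **Primary model** (Statistical methods {20a}, Effectiveness). The method is multilevel: "Multilevel modelling will be used to assess the improvement of case management participants over time compared to care as usual". The terms are then listed: "Primary analysis involves entering time, group and their interaction (exposure) as fixed terms". The levels are not named, and neither region, hospital nor the baseline score is among the terms.
- **Sensitivity model** (same section). "Sensitivity analysis will be performed by extending the resulting models with covariates, controlling for the effects of age, gender and level of education". The next sentence is the retention rule: "Covariates will be kept in the model as long as they contribute significantly to the model".
- **Region.** Under Care as usual: "The usual care differs depending on the regional structures and collaborations". Under The case manager: "The case managers form three teams, one in each region", and the teams are not alike: "Two of the teams include a peer support worker".
- **Allocation.** Sequence generation {16a} describes 1:1 allocation "using a computerized random schedule, in blocks of six". Neither that section, Trial design {8} nor Implementation {16c} names a stratification factor.
- **Baseline score.** Sample size {14} says the pre-intervention measurement will be a predictor in the model. On that ground it multiplies 194 by (1 − 0.5²) to reach 146, then allows 30% drop-out to reach 209.

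**The concern.** Three choices in the effectiveness analysis are fixed badly or do not match the rest of the article.

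First, a sensitivity analysis should show whether the result survives a stated change of model. Here the change is not stated in advance, because it depends on which of three demographic variables reach significance. The set may differ between HADS total, its subscales, USER-P, LiSat, PAM, LUNS and the family outcomes, so the adjusted results would not be comparable. If all three covariates drop out, the sensitivity model is the primary model.

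Second, the article itself says that both the comparator and the delivery of the intervention vary by region. A term that may explain outcome variance, and whose balance between arms is not described as protected by the randomisation, is left out.

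Third, the sample size takes credit for a baseline covariate that the primary model does not list.

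At stake are the interpretability of the adjusted results, some precision, and agreement between the planned sample size and the planned model.

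**Working it through.** **1. The plan's own figures.** Inputs from Sample size {14}: base N 194, R = 0.5, drop-out 30%.

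- 194 × (1 − 0.5²) = 194 × 0.75 = 145.5, rounded up to 146.
- 146 / (1 − 0.30) = 208.6, rounded up to 209.

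Both are reproduced. (The base figure of 194 is matched by a t-test at one-sided 5%, with 97 per arm; a two-sided 5% test needs 244. That is a separate matter and is not used below.) Without the baseline term the same chain gives 194 / 0.70 = 277.1, or 278 to recruit. The baseline covariate therefore carries 278 − 209 = 69 participants of the plan.

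**2. Does selection by significance distort the test?** A simulation used 146 participants, three covariates, backward elimination at p > 0.05 and 4,000 replicates per setting (Monte Carlo SE about 0.35 percentage points). The covariates ranged from unrelated to strongly predictive.

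| Analysis | Type I error for the group effect |
|---|---|
| All three covariates kept | 5.0–5.7% |
| Covariates selected by significance | 4.9–5.9% |
| Either the unadjusted or the selected model counted as positive | 5.0–8.1% |

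Selection alone is not distinguishable from a fixed set. The last row would matter only if the trial could be declared positive on either model.

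**3. How often would the sensitivity model collapse?** If none of the three covariates is related to the outcome, and each is tested at 5% as one independent term, all three drop out with probability about 0.95³ = 0.86. The sensitivity result would then be a copy of the primary one.

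**4. What does a region term gain?** The documents give no between-region variance, so the share of outcome variance explained by region, r, is assumed. Starting from 80% power at two-sided 5%, power with region in the model is Φ((1.960 + 0.842)/√(1 − r) − 1.960).

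| Assumed r | Power |
|---|---|
| 1% | 80.4% |
| 2% | 80.8% |
| 5% | 82.0% |
| 10% | 84.0% |

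**5. How large could chance imbalance be?** Assume three equal regions and 146 analysed participants, 73 per arm. The between-arm difference in one region's share has SD √((1/3)(2/3)(2/73)) = 0.078, and 1.96 × 0.078 = 0.153. With all 209 recruited the values are 0.065 and 0.128. A simulation of a single list in blocks of six, with 209 participants, gave a worst-region departure from 50% allocation with median 5.6 and 95th percentile 11.6 percentage points.

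The shift in the estimated effect is imbalance × regional difference. The regional difference is assumed, and it must be a difference in change or in baseline-adjusted HADS. A stable difference in level largely cancels from a contrast in change.

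| Assumed regional difference | Shift at 1 SD imbalance | Shift at the 95% limit |
|---|---|---|
| 1 HADS point | 0.08 | 0.15 |
| 2 HADS points | 0.16 | 0.31 |
| 3 HADS points | 0.23 | 0.46 |

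For scale, the planning SD is 3.25/0.36 = 9.03. With R = 0.5 the residual SD is 9.03 × √0.75 = 7.82, and the standard error of the effect is 7.82 × √(2/73) = 1.29. The largest entry is 0.46/1.29 = 0.36 standard errors.

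**The case against.** The strongest reply is that nothing here threatens the headline result. A reader of the retention rule might infer that the primary effect is picked by p-values. It is not: the primary model is fixed in advance, and the rule governs only the extended models. Nor does the article allow a claim of success on whichever model is favourable, so the 8.1% in the last row of the type I error table describes no procedure in the plan. This part of the reply stands.

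A reader might also infer that leaving out region biases the comparison. It does not. Region is not described as a stratification factor, participants are randomised within one scheme, and chance imbalance is already covered by the standard error. A shift of about 0.4 points arises only by pairing an extreme imbalance with an assumed regional difference of 3 points, nearly the whole 3.25-point target.

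It is fair to add that the absence of stratification is read from silence, that the unnamed levels of the multilevel model could include region, and that such detail may sit in the full protocol or SAP. But the article lists its primary fixed terms and its candidate covariates, and region is in neither list. Injury type and length of stay are used in the planned subgroup analyses {20b}; not using them as covariates is no error.

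On baseline, one could say that it enters as the first repeated measurement. That is not what Sample size {14} describes, and it does not earn the same credit. If the arms are free to differ at baseline, the contrast in change at one follow-up has relative variance 2(1 − R) = 2 × 0.5 = 1.0, against 1 − R² = 0.75.

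The reply does not rescue the retention rule. It is a stated decision, which an SAP could repair only by departing from it.

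**Conclusion.** The point holds in a limited form. The retention rule makes the sensitivity analysis data-dependent, possibly different across outcomes, and possibly identical to the primary analysis. The harm is to its usefulness; the effect on type I error is small.

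Omitting region forgoes modest precision (0.4 to 4.0 percentage points of power, for an assumed 1–10% of variance) and leaves chance regional imbalance unadjusted. It introduces no bias. The shift table depends on equal regions and on regional differences that the documents do not supply, so it should be read only as a range.

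The mismatch over baseline HADS rests on no assumption. One section uses it to reduce the sample size by a quarter, and the other does not list it in the primary model.

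**What to change.** In the SAP, and in the effectiveness text of {20a}:

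- Delete the keep-if-significant sentence. Keep age, gender and education in the sensitivity model for every outcome, whatever their p-values.
- Enter baseline HADS in the primary model, as Sample size {14} already says. State that the modelled outcomes are then the follow-up assessments, and which group contrast is the treatment effect.
- Add region/hospital to the primary model as a three-level fixed effect; three units are too few for a random effect. Name the levels of the multilevel model.
- State whether the allocation list was stratified by hospital. The region term is appropriate in either case.

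No new data are needed: recruiting hospital is known and the other variables are collected at baseline or from hospital records. The cost is two degrees of freedom for region and one for baseline, out of about 146 analysed participants, plus the wording change. If region explains nothing, the loss of precision is negligible.

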#### Cost-effectiveness and cost-utility

The trial-based economic evaluation will involve a combination of a cost-effectiveness analysis (CEA) and a cost-utility analysis (CUA). Effects will be presented as clinical outcomes (i.e. self-efficacy and psychosocial well-being). In these CEAs, the incremental cost-effectiveness ratio (ICER) will be expressed as the incremental costs per point improvement on the primary outcome measure. The primary outcomes measure for the CUA will be quality-adjusted life years (QALYs), based on the EuroQol (EQ-5D-3L). The EQ-5D-3L can distinguish between different health states. For each of the different states, a weight is contributed based on the valuation given by the general population (Euroqol group). These range from 0 (representing death) to 1 (representing full health). Cost-effectiveness evaluations make use of these utilities. In the CUA, the ICER will be expressed as the incremental costs per QALY. This economic evaluation will be performed from a societal perspective, which implies that all relevant costs and outcomes will be considered. The time horizon will be the same period as the follow-up period of the trial.

Total costs will be estimated using a bottom-up (or micro-costing) approach, where information on each element of service used is multiplied by an appropriate unit cost and summed to provide an overall total cost. The economic evaluation will assess not only the intervention costs, but also healthcare costs, patient and family costs, and costs outside the health care sector. For this study, we have developed a cost questionnaire, based on existing questionnaires which will identify all relevant costs aspects.

Despite the usual skewness in the distribution of costs, the arithmetic means will be generally considered the most appropriate measures to describe cost data. In case of skewness of the cost data, non-parametric bootstrapping will be used to test for statistical differences in costs between the case management and care as usual group. The bootstrap replications will be used to calculate 95% confidence intervals (CI) around the costs (95% CI). If cost data are distributed normally, *t*-tests will be used. The robustness of the ICER will be checked by non-parametric bootstrapping (1000 times). Bootstrap simulations will also be conducted in order to quantify the uncertainty around the ICER, yielding information about the joint distribution of cost and effect differences. The bootstrapped cost-effectiveness ratios will be subsequently plotted in a cost-effectiveness plane, in which the vertical line reflects the difference in costs and the horizontal line reflects the difference in effectiveness. The choice of treatment depends on the maximum amount of money that society is prepared to pay for a gain in effectiveness, which is called the ceiling ratio. Therefore, the bootstrapped ICERs will also be depicted in a cost-effectiveness acceptability curve showing the probability that case management is cost-effective using a range of ceiling ratios.

#### Feasibility

Registration forms, evaluation forms and written notes of supervision meetings will be analysed descriptively, and focus groups will be analysed qualitatively. Audio and videotapes of all focus group interviews will be transcribed verbatim. Analyst triangulation will be applied [76]; the transcripts and observations combined with additional notes that will be taken during the focus group interviews will be analysed independently by two researchers using the qualitative analysis software ATLAS.ti (version 7.0). An inductive content analysis approach will be adopted [77], in which common themes and categories emerge using inductive reasoning and constant comparison. The texts will be thoroughly read and open codes will be applied to describe all aspects of the content [78]. Codes referring to the same phenomenon will be grouped into categories and these categories will be grouped into higher-order themes. Categories and themes will be combined into general statements to describe the phenomenon [77]. Discrepancies in coding and interpretation will be discussed in a meeting together with a third researcher to reach consensus regarding the categories and themes. The video recordings will be compared with the written transcripts to be able to identify potentially relevant additional non-verbal information or cues presented by the participants. Quotations will be selected based on representativeness of the emerged themes by the coordinating researcher and verified by the other two researchers.

#### Other study parameters

Demographic and injury-related characteristics will be analysed descriptively.

### Interim analyses {21b}

No interim analyses are planned because there are no anticipated risks to participation in this study.

### Methods for additional analyses (e.g. subgroup analyses) {20b}

Subgroups will be formed based on type of injury (stroke vs. other types) and severity, for which length of hospital stay will be used as a proxy (based on the distribution of the sample). Even though the subgroups are likely to be too small to draw firm conclusions, we will analyse this exploratively because the usual care for stroke is already better organized than for other types of brain injury (possibly lowering the additional gains of case management over care as usual for stroke compared to other types of brain injury) and because those with moderate to severe ABI may have more to gain from case management than those with mild ABI.

### Methods in analysis to handle protocol non-adherence and any statistical methods to handle missing data {20c}

Data will be analysed by the intention-to-treat approach. Sensitivity analysis will be performed with regard to missing data; we will evaluate which of the measured variables are associated with missing outcomes and will include these in the model. Reasons for drop-out or missing assessments will be documented if participants are willing to share this.

### Plans to give access to the full protocol, participant level-data and statistical code {31c}

The full protocol, anonymized data set and statistical code will be available on request after the results of the study have been published.

## Oversight and monitoring

### Composition of the coordinating centre and trial steering committee {5d}

#### Principal (CMvH), coordinating investigators (APMS; CR interim)

Design of the study;Preparation of protocol and revisions;Ethics committee application;Study planning;Recruiting, training and supervising research assistants;Responsible for trial master file;Provide annual reports to ethics committee;Data verification;Publication of study reports;

#### Project team

Principal (CvH) and coordinating (APMS; CR interim) investigators, overall project leader (JZ), intervention project leader (NJ), ReMinder monitoring tool project leader (KJ, MD)
Agreement of final protocol;Recruiting hospital staff and assistance with recruiting procedures;Implementing ReMinder;Entering participants in case management group into monitoring tool;Recruitment, training and supervising case managers;Collecting registrations of case management activities;Organizing project team meetings.

### Composition of the data monitoring committee, its role and reporting structure {21a}

Because of the low burden and minimal risks, no data monitoring committee was appointed.

### Adverse event reporting and harms {22}

We will only report those adverse events that are directly related to our study, defined as experiencing negative consequences of case management in terms of psychosocial well-being or self-management that are reported spontaneously by the subject. Due to the non-invasive nature of this study, no experiment-related (serious) adverse events are expected.

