**Methods:**

This is a pragmatic randomized controlled superiority trial with two parallel groups and repeated measures in adults with ABI and their family, taking place between November 2019 and December 2021 in three provinces in the Netherlands. Participants will be randomly allocated to either the case management group, receiving case management from hospital discharge up to 2 years thereafter, or the control group, receiving care as usual. Effectiveness will be evaluated every 6 months for 18–24 months by patient-reported psychosocial well-being (Hospital Anxiety and Depression Scale (HADS), Utrecht Scale for Evaluation of Rehabilitation-Participation (USER-P) restriction subscale and the Life Satisfaction Questionnaire (LiSat)), self-management (Patient Activation Measure (PAM)) and care needs (Longer-term Unmet Needs after Stroke (LUNS)). Family outcomes include self-efficacy (Carer Self-Efficacy Scale (CSES)), caregiver burden (Caregiver Strain Index (CSI)), psychosocial well-being (LiSat, HADS), family needs (Family Needs Questionnaire (FNQ)). Feasibility will be evaluated using qualitative methods, assessing fidelity, dose delivered, dose received, reach, recruitment and context. Cost-effectiveness will be determined by the EQ-5D-3L and service use.

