### Trial design {8}

This is a pragmatic prospective randomized controlled superiority trial with two parallel groups and repeated measures. Randomization will be performed as block randomization with a 1:1 allocation.

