##### Outcomes for people with ABI

Psychosocial well-being will be assessed using the HADS, the Utrecht Scale for Evaluation of Rehabilitation-Participation (USER-P [49]) restriction subscale and the Life Satisfaction Questionnaire (LiSat [52]). The HADS consists of 14 items scored on a 4-point scale ranging from 0 to 3 with varying anchors. Total scores can be calculated for the full scale (primary outcome). The two subscales (anxiety and depression) will also be computed and analysed as secondary outcomes; subscale scores of > 7 suggest the presence of an anxiety disorder or depression. The psychometric quality of the scale is sufficient [53]. The USER-P restriction subscale consists of 9 items asking about restrictions in vocational, leisure and social activities as a consequence of ABI. Items are rated on a scale from 0 (not possible) to 3 (without difficulty) and a ‘not applicable’ option. The total score ranges from 0 to 100 based on the number of applicable items; higher scores indicate less restrictions in participation. The scale has shown sufficient reliability and validity [49]. The LiSat assesses various aspects of life satisfaction including life as a whole, self-care management, contacts with friends, vocational, family life, partner relationships, financial situation, leisure situations and sex life. The nine items are scored on a ﻿6-point scale ranging from ‘very dissatisfied’ to ‘very satisfied’. The scale has satisfactory reliability and validity [54, 55].

The concept of self-efficacy, one’s confidence in the ability to deal with (health) problems, will be measured as a proxy for self-management, since self-efficacy is a prerequisite for behavioural change. Self-efficacy will be measured with the Patient Activation Measure (PAM [56];), which is a 13-item instrument assessing self-reported knowledge, skills and confidence for self-management of one’s health or chronic condition. Items are scored on a scale of 0 (disagree strongly) to 4 (agree strongly) and a not applicable option. An algorithm is available to transform the scores on the PAM to different levels of self-management, from ‘disengaged and overwhelmed’ to being their own health advocate. The PAM requires a license and sharing of the de-identified data with Insignia Health. The Dutch version of the PAM has shown moderate test-retest ability (*r* = 0.47) [57].

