#### Cost-effectiveness and cost-utility

Cost-effectiveness and cost-utility will be determined using the EuroQol (EQ-5D-3L) and a service use questionnaire, included in the assessments on baseline and after 6, 12, 18 and 24 months. The EQ-5D-3L [68] consists of five questions measuring health status. The dimensions covered are mobility, self-care, daily activities, pain or discomfort, and anxiety or depression. These domains are rated as ‘no problem’, ‘moderate problem’ or ‘unable to do’. The EQ-5D-3L has shown good measurement properties [69]. Service use will be measured with a self-report cost questionnaire, which was constructed to collect cost data from a societal perspective. It is based on the steps described by Thorn and colleagues [70] and on the questionnaire used by Rauwenhoff and colleagues [71].

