### Sample size {14}

Power calculation was based on the primary outcome measure Hospital Anxiety and Depression Scale (HADS). A study evaluating a monitoring/psycho-educational intervention in patients with possible ABI due to cardiac arrest showed to be effective in improving both anxiety and depressive symptoms with a group difference on the HADS of 3.25 points, corresponding to Cohen’s *d* effect size of 0.36 [73]. With an alpha of .05 and power value of 80%, a sample size of 194 is required to detect such between-group effect in the post-intervention measurement. This number can be adjusted for the correlation between baseline and follow-up data, since baseline measures will be entered in the model as an independent variable, by multiplying the sample size by 1 − *R*^2^ (R is the population correlation between the dependent variable (post-intervention) and the pre-intervention measurement) [74]. *R* is estimated to be at least 0.5, making the sample size 194 × (1 − 0.5^2^) = 146. Taking a drop-out rate of 30% into account, at least 209 people with ABI should be recruited. For each participating person with ABI, the family member who is or would be acting as the informal caregiver will be asked to be enrolled in the study as well. The number of participating family members will not exceed the maximum of 209.

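### Adverse events are defined so that only the case management arm can have one, so they cannot be compared between arms, and a minority who deteriorate may go unseen

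*Protocol article*

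**What the plan says.** The protocol article's section Adverse event reporting and harms {22} sets the rule: "We will only report those adverse events that are directly related to our study, defined as experiencing negative consequences of case management". The sentence then limits both the type of event and how it is found: "in terms of psychosocial well-being or self-management that are reported spontaneously by the subject". The section adds that "no experiment-related (serious) adverse events are expected".

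The abstract's Methods paragraph describes the two arms as one "receiving case management from hospital discharge up to 2 years thereafter, or the control group, receiving care as usual". Care as usual contains no case management.

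Other sections describe data that do not depend on arm. All participants receive questionnaires every six months (Participant timeline {13}). People with ABI complete the HADS, USER-P restriction subscale, LiSat and PAM. Family members also complete the HADS (Family member outcomes). For the HADS, the article gives a threshold: "subscale scores of > 7 suggest the presence of an anxiety disorder or depression". Under Cost-effectiveness and cost-utility: "Service use will be measured with a self-report cost questionnaire". Effectiveness is analysed with a multilevel model containing time, group and their interaction (Statistical methods {20a}).

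**The concern.** An event must pass three tests to be reported: it is a consequence of case management, it concerns well-being or self-management, and the participant raises it unprompted. The first test excludes every control participant. The result is a count for one arm with no comparator.

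Reporting channels also differ. Participants in the case management arm can put a question to a case manager at any time (Monitoring tool), and only they complete evaluation forms (Plans for assessment and collection of outcomes {18a}). Controls have neither.

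Harm in the named domains is conceivable. The intervention asks people every three months whether they have problems from their brain injury, and sends reminders until they open the questionnaire. This could unsettle some of them. Without a symmetric count, the trial can neither show that nor give reassurance about how many individuals deteriorate. No data monitoring committee and no interim analysis are planned, both on the ground of low or absent risk, so no other body is set up to look at this by arm.

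**Working it through.** The article states no adverse event figure, so there is none to reproduce. The check has three parts.

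**1. Apply the definition to each arm.**
- Case management arm: an event can qualify if it is linked to case management and volunteered.
- Control arm: no exposure to case management, so the first condition is never met. The count is 0 for any true rate of deterioration.

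**2. What the rule would show if there were no true difference.** Inputs: "at least 209 people with ABI should be recruited" (Sample size {14}) and "Randomization will be performed as block randomization with a 1:1 allocation" (Trial design {8}), so 209/2 ≈ 104 per arm. Assumed, because the article gives no rates: true worsening p = 5% to 20%, equal in both arms, and a share q = 10% to 50% of those events that are linked to case management and volunteered.

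Expected reported events = n × p × q.
- Low end: 104 × 0.05 × 0.10 = 0.5 in the case management arm, 0 in control.
- High end: 104 × 0.20 × 0.50 = 10.4 in the case management arm, 0 in control.

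The difference of 0.5 to 10.4 events comes wholly from the definition.

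**3. What a symmetric count could show.** The 95% confidence interval half-width for a difference in proportions with equal rates is 1.96 × √(2p(1 − p)/n). Three values of n per arm, for people with ABI:
- 104: everyone recruited (209/2).
- 73: completers, from the article's 146 (146/2).
- 44: completers with a baseline subscale score of 7 or below, if 60% qualify (assumed): 0.6 × 73 = 43.8.

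| Assumed worsening rate | n = 104 | n = 73 | n = 44 |
|---|---|---|---|
| 10% | ±8 points | ±10 points | ±13 points |
| 20% | ±11 points | ±13 points | ±17 points |
| 30% | ±12 points | ±15 points | ±19 points |

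For the 20% row: 1.96 × √(0.32/104) = 0.109; 1.96 × √(0.32/73) = 0.130; 1.96 × √(0.32/44) = 0.167. For the other rows, 2p(1 − p) is 0.18 and 0.42.

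Power at two-sided 5%, again with assumed rates:

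| Rates compared | n = 104 per arm | n = 73 per arm |
|---|---|---|
| 5% v 10% | 28% | 21% |
| 10% v 20% | 52% | 39% |
| 20% v 30% | 38% | 28.5% |

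So a symmetric table would be descriptive, not a test.

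**The case against.** The strongest reply is that the domains named in the adverse event definition are already measured in everyone. The HADS total is the primary outcome, its two subscales are secondary outcomes, and USER-P, LiSat and PAM are compared between randomised arms. If case management worsened distress on average, the primary analysis could show it. This stands. A reader might infer from the adverse event section that harm cannot be compared at all, and the documents do not support that. What is lacking is a comparison of adverse events, and any stated count of individuals who deteriorate. The article's Discussion concedes that people with mild injury who recover anyway may mask effects in a more severe group. The same masking can apply to harm.

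A second reply is that a deterioration table belongs in the analysis plan, which is not shown. That is fair for the table, and such a table would not contradict the article. It does not answer the rule itself, which the article states and limits with the word only.

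A third reply is that the usual harm items may not exist in the data. This also stands. The article does not list deaths as a collected item, and the items of the service-use questionnaire are not shown. Service use is also ambiguous as a harm measure: case management aims to ease access to services, and the Discussion expects costs to rise at first.

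**Conclusion.** The point holds in a limited form. By a stated rule, the control arm's adverse event count is 0, so adverse events cannot be compared between arms. Harm would be visible only as worse average scores on the efficacy questionnaires, which can hide a minority who deteriorate. The primary efficacy result is unaffected, and the remedy is a cheap improvement.

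Two further inferences should not be drawn. First, the article does not plan a comparative safety conclusion from this count; the risk is that a low count is later read as one. Second, the article does not say who judges whether an event is related to the study, so it cannot be said that the participant makes that attribution. The structural zero does not depend on who judges.

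The zero follows from the wording alone. The event counts, interval widths and power figures rest on assumed rates and, for n = 44, on an assumed 60% with a baseline subscale score of 7 or below.

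**What to change.** 1. Keep the spontaneous reports, but state that they are a one-arm count that supports no comparative safety statement.
2. Add a descriptive table by randomised arm, separately for people with ABI and family members. It gives the number whose HADS anxiety or depression subscale was 7 or below at baseline and above 7 at follow-up. Use 6, 12 and 18 months, which are common to all participants; only some reach 24 months. Give the denominator assessed in each arm, and a confidence interval for the difference.
3. Add deaths and hospital or emergency use only if the follow-up records and the service-use questionnaire capture them. Read service use with care, because more use may be an intended effect.

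The cost is one sentence and one table. The HADS part needs no new assessment. The downsides are that background deterioration unrelated to the trial will appear in both arms, that people already above 7 at baseline on a subscale cannot contribute a new crossing on it, and that precision is too low for more than description.
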